# DATA MANAGEMENT

See Appendix 29 for the complete data management plan.

## **Data collection**

All data will be handled and stored securely and in compliance with the Data Protection Act and GDPR.

Personal information relating to contact details will be collected when participants provide informed consent to participate in the full study. Participants will be identified by a unique participant ID, and files linking participant ID to their contact details will be held on the University of the West of England OneDrive for Business, which is compliant with GDPR, ISO27001 and Cyber Essentials.

## Participants will complete several self-report quantitative and qualitative measures at different assessment time points throughout the study (see 5.6 and Table 1). This data will be collected online via Qualtrics (whereby participants are sent the appropriate weblink), a secure online survey platform. Qualtrics uses Transport Layer Security (TLS) encryption (also known as HTTPS) for all transmitted data. This data will be downloaded into SPSS (a statistical software package) and NVivo (a qualitative data analysis software package) with files held on OneDrive for Business.

## If participants complete these measures by paper, they will be sent these in the post with a stamped pre-addressed envelope to return to the research team. Once returned, these will be stored in a locked filing cabinet in a locked office at the University of the West of England. Once the data is inputted directly into SPSS and NVivo files on OneDrive for Business, the paper versions will be securely destroyed.

Anonymised data related to ABC attendance and engagement, as well as recordings of the sessions, will be collected by programme facilitators. This data will be shared with the research team via OneDrive for Business, which will then be copied over onto the University of the West of England OneDrive for Business.

Participants taking part in the recorded interviews will be given a pseudonym, and thus will not be identifiable. The recordings via Teams will be saved into a file on the University of the West of England OneDrive for Business, and once transcribed, they will be deleted.

Other quantitative data collected throughout the trial (e.g., withdrawal rates) will be collected by the research team and saved in a file on OneDrive for Business.

## **Access to Data**

Personal information relating to participant contact details, and files linking participant ID to their contact details, will only be accessed by the Study Manager and CI.

All other data files will only be accessed by the research team, with any sharing of data files between the team completed via password-protected university OneDrive files.

Direct access will be granted to authorised representatives from the Sponsor, host institution and the regulatory authorities to permit trial-related monitoring, audits, and inspections- in line with participant consent.

- 1. Archiving

All study documentation will be archived for a minimum of 10 years following the end of the study at the University of the West of England.

# ETHICAL AND REGULATORY CONSIDERATIONS

# HRA Approval

Prior to the enrolment of participants, the Health Research Authority (HRA) and NHS Research Ethics Committee (REC) must provide written approval of the conduct of the study, the protocol, all participant-facing materials, study advertisements, and participant compensation. (IRAS: 327507, REC ref: 24/NE/0092, HRA approval date: 05/06/2024)

- 1. **University REC Approval**

Following HRA approvals, the study will also be approved by the appropriate REC within the University of the West of England. (Approval date: 20/06/2024, Project Number: CHSS.24.06.222)

- 1. **Amendments**
     1. **Substantial Amendments**

As outlined in the HRA Non-CTIMP Standard Conditions, a substantial amendment is any amendment to the terms of the application for ethical review, or to the protocol or other supporting documentation approved by the REC that is likely to affect to a significant degree:

(a) the safety or physical or mental integrity of the research participants

(b) the scientific value of the research

(c) the conduct or management of the research, including its ongoing legality and feasibility.

Any substantial amendment will be submitted for approval through IRAS. Once the substantial amendment has been approved by NHS REC, the CI will inform the University REC of the amendment. The substantial amendment will not be implemented until approval is granted by both NHS and University REC.

Updated versions of the protocol and any other documents will be recorded in the version control table in Appendix 30.

- - 1. **Minor Amendments**

Minor amendments do not require NHS REC approval. Such amendments will be submitted to the University of the West of England REC for approval prior to being implemented.

- 1. **Good Clinical Practice**

The study will be conducted in accordance with the principles of Good Clinical Practice (GCP). Members of the study team who have contact with participants will complete the full GCP course prior to the start of the study and complete a refresher every two years as needed.

- 1. **Protocol Violations and Serious Breaches**

All deviations or violations from the protocol will be reported to the Chief Investigator who will report such incidents to the trial management and steering committees. The trial management and steering committees will assess whether amendments or other action (e.g. further training for research staff) is needed to address such protocol deviations or violations.

In accordance with the HRA Non-CTIMP Standard Conditions, a serious breach is defined as a breach of the protocol or, of the principles of Good Clinical Practice which is likely to affect to a significant degree the safety or physical or mental integrity of the research participants, or the scientific value of the research. The Sponsor will be notified within 24 hours of identifying a likely Serious Breach. If a decision is made that the incident constitutes a Serious Breach, the incident and agreed action plan will be reported to the NHS REC.

- 1. Financial and other competing interests

The Chief Investigator, study management group members, steering committee members, and other individuals involved in the study have no financial or competing interests regarding the conduct, results, or outcomes of this study.

- 1. Insurance indemnity

The conduct of this study is covered by the insurance arrangements of the University of the West of England, which includes Employers Liability Insurance and Public Liability insurance.

- 1. **Care during and following the study**

Control participants will be given the 77-page Macmillan body image booklet, which provides a substantial amount of support and guidance relating to managing body image concerns. Further, given that there is no current ‘treatment-as-usual’ in relation to body image support for women treated for breast cancer, this booklet may constitute the first time that these women have received support specifically relating to body image, and may even reduce distress.

Intervention participants may experience distress during the sessions, given the sensitive nature of the content relating to body image and its impacts (e.g., on relationships). However, any distress will be managed by the ABC facilitators, who have a great deal of experience in supporting women treated for breast cancer.

Completing the self-report outcome measures may evoke distress for participants, due to the sensitive nature of the items (e.g., relating to body image and sexual wellbeing). However, this risk is outlined in the PIS (Appendix 2), which also includes signposting to various cancer support organisations and general mental health support organisations. Participants will also be reminded that they can stop completing the questionnaires at any point or skip any questions. Further, PPI advisors reviewed, reduced, and refined the number of provisional outcome measures. They also felt that the measures and comprising items were appropriate and reflected the impact of their body image concerns. Therefore, whilst these items might evoke distress among participants, this is outweighed by the potential for the research to indicate evidence that ABC improves body image distress and associated impacts.

A subsample of participants will be interviewed at different points throughout the study, to explore their experience and feedback on all aspects relating to the research process (e.g., the recruitment process, randomisation). Whilst these interviews (Appendices 11-16) are not focused on the participants’ own body image, there is still the risk of distress. However, this risk is outlined in the PIS (Appendix 2), which also includes signposting to various cancer support organisations and general mental health support organisations. Participants will also be reminded that they do not have to answer any questions they do not feel comfortable answering and that they can stop the interview at any time. A distress protocol will be followed, whereby the interview will be paused and subsequently terminated if required.

For participants in the intervention arm, the final session of ABC covers managing future setbacks relating to body image, thereby equipping participants with self-management tools they can use once the study ends. All participants (including intervention and control) will be provided with the Macmillan body image booklet and will be signposted to appropriate support at all data collection timepoints.

- 1. **End of Study**

For safety reporting and regulatory purposes, the end of the study will be when all data collection is complete, and data is finalised (e.g. transcripts complete). The REC will be informed about the end of the study within 90 days of the final follow-up visit taking place.

1. **STUDY MANAGEMENT**
   1. **Study Management Group**

The Study Management Group (SMG) comprises [name] (CI), [name] (Study Manager), [name], [name], [name], [name], and [name]. The Study Management Group will meet monthly to discuss the progress and management of the project, whilst [name] and [name] will be responsible for the day-to-day management of the study.

- 1. **Study Steering Committee**

The Study Steering Committee (SSC) comprises the SMG and the following seven independent members:

- [name] (Independent Chair)
- [name] and [name] (Breast Cancer Survivors)
- [name] (Clinical Psychologist)
- [name] (Psycho-Oncology Researcher)
- [name] (Associate Director of Services and Service Improvement – Breast Cancer Now) and
- [name] (Chief Nursing Officer – Macmillan Cancer Support)

The SSC will meet up to three times a year and are responsible for the overall oversight of the project. This includes ensuring that the study is conducted to rigorous ethical and scientific standards, that the protocol is followed, and is on schedule.

- 1. **Public and Patient Involvement (PPI)**
     1. **PPI co-applicant**

The study has a PPI lead and co-applicant ([name]). She has been extensively involved in the development and refinement of the study proposal. In the study, she will be responsible for co-chairing the PPI group and will attend all SMG meetings.

- - 1. **PPI group**

There has been PPI involvement throughout every stage of the development of ABC and its preliminary evaluation. Women treated for breast cancer, associated health professionals (e.g., cancer nurse specialists, psychologists) and cancer support organisations (e.g., Breast Cancer Now) contributed to the adaptation of the original intervention and its acceptability testing.

Prior to the grant submission, a PPI group of women treated for BC from diverse backgrounds (regarding age, sexual orientation, ethnicity, geographic location, socio-economic status, stage of treatment/recovery) informed several aspects of research design, such as the participant eligibility criteria, the control arm, the self-report validated outcome measures, and data collection formats.

A study PPI group has been assembled, comprising women treated for BC of different ages, ethnicities, sexual orientations, geographical locations, and socio-economic backgrounds, plus representatives from cancer organisations, including those supporting underserved groups (e.g., Black Women of Colour for people of colour). The Six UK Standards for Public Involvement are being followed. For example, the group meet online to facilitate accessibility, they have already contributed to decision making, and they are being reimbursed for each meeting. Training and support will be delivered to the PPI lead and PPI group to develop their research knowledge skills (e.g., via online training, conference attendance; NIHR resources for public involvement).

The study PPI group will meet online up to three times a year and have already advised on research protocols and participant-facing materials (e.g., PIS, ICF). Throughout the project, their input will be involved in the following activities: advising on strategies to maximise recruitment, engagement and retention; advising on culturally and ethnically relevant issues as necessary; helping conduct interviews, help interpret research findings; advising on research reports; selecting specific outlets for dissemination; designing and producing summary reports for key parties, including research participants; and designing and delivering presentations to national cancer organisations or at academic conferences.

The SSC also includes two women with lived experience of BC cancer and two representatives from national cancer support organisations (see 10.2).

### APPENDICES

The below table includes a list of study documents and patient-facing materials and documents their versions and associated dates.

| **Appendix No.** | **Document Title** | **Version No.** | **Date** |
| --- | --- | --- | --- |
| 1 | ABC Patient Invitation General + Expression of Interest Form | 1 | 18/04/2024 |
| 2 | ABC Main Study Participant Information Sheet | 2 | 23/05/2024 |
| 3 | ABC Poster | 1 | 18/04/2024 |
| 4 | ABC Patient Invitation Leeds + Expression of Interest Form | 1 | 18/04/2024 |
| 5 | ABC Social Media Post | 1 | 18/04/2024 |
| 6 | ABC Main Study Consent Form | 1 | 18/04/2024 |
| 7 | ABC Interview Participant Information Sheet | 2 | 23/05/2024 |
| 8 | ABC Interview Consent Form | 1 | 18/04/2024 |
| 9 | ABC Programme Feedback (Rating Scales + Open-ended Questions) | 1 | 18/04/2024 |
| 10 | ABC Research Process Feedback (Rating Scales + Open-ended Questions) | 1 | 18/04/2024 |
| 11 | Interview Schedule: Did Not Consent | 1 | 18/04/2024 |
| 12 | Interview Schedule: Dropped Out Post-Randomisation | 1 | 18/04/2024 |
| 13 | Interview Schedule: Control Participants Dropped Out During Study | 1 | 18/04/2024 |
| 14 | Interview Schedule: Intervention Participants Dropped Out During Study | 1 | 18/04/2024 |
| 15 | Interview Schedule: Control Participants Finished Study | 1 | 18/04/2024 |
| 16 | Interview Schedule: Intervention Participants Finished Study | 1 | 18/04/2024 |
| 17 | Demographic and Breast Cancer Information | 1 | 18/04/2024 |
| 18 | Kessler Psychological Distress Scale | n/a | |
| 19 | Body Appreciation Scale-2 | n/a | |
| 20 | Functional Assessment of Cancer Therapy – Breast: Breast Cancer Subscale | n/a | |
| 21 | Hopwood Body Image Scale | n/a | |
| 22 | BREAST-Q: Sexual Well-Being Scale | n/a | |
| 23 | Modified version of the Adult Service Use Schedule: T1 | 1 | 18/04/2024 |
| 24 | Modified version of the Adult Service Use Schedule: T3 | 1 | 18/04/2024 |
| 25 | Modified version of the Adult Service Use Schedule: T4 | 1 | 18/04/2024 |
| 26 | EQ-5D-5L | n/a | |
| 27 | Recovering Quality of Life-Utility Index | n/a | |
| 28 | Work and Social Adjustment Scale | n/a | |
| 29 | Data Management Plan | 1 | 16/04/2024 |
| 30 | Protocol Amendment History | n/a | |
| 31 | Follow-up ABC Acceptability questions | n/a | |
| 32 | Additional Demographics Question | n/a | |

**12.1 Appendix 1: ABC Patient Invitation General + Expression of Interest Form**

[figure not shown]

ADD NHS TRUST LOGO HERE

ADD NHS TRUST PI’s DETAILS HERE

**12.3 Appendix 3: ABC Poster**

**12.4 Appendix 4: ABC Patient Invitation Leeds + Expression of Interest Form**

[figure not shown]

**12.9 Appendix 9: ABC Programme Feedback (Rating Scales + Open-ended Questions)**

**ABC Feedback**

Now that you have finished attending ‘Accepting your Body after Cancer’, we would appreciate your feedback on the programme.

This feedback is very valuable, as it will help us improve the programme if necessary. Therefore, please be as honest as possible. Don't forget - your responses are anonymous!

First of all, how **helpful** did you find the programme overall?

|  | Not at all helpful  1 | 2 | 3 | 4 | Very helpful  5 |
| --- | --- | --- | --- | --- | --- |
| Please select one option: |  |  |  |  |  |

Would you like to tell us more about this?

How **helpful** did you find the CBT approach and strategies in the programme?

|  | Not at all helpful  1 | 2 | 3 | 4 | Very helpful  5 |
| --- | --- | --- | --- | --- | --- |
| Please select one option: |  |  |  |  |  |

Would you like to tell us more about this?

What **topics and/or exercises** covered in the programme did you find the **most** helpful?

What **topics and/or exercises** covered in the programme did you find the **least** helpful (if any)?

Were there any **topics** that you felt were **missed** in the programme?

You are now going to be asked some questions about the format and content of ABC.

What did you think about the **length** **of the overall programme** (7 sessions)?

|  | Too short  1 | The right length  2 | Too long  3 |
| --- | --- | --- | --- |
| Please select one option: |  |  |  |

What did you think about the **length** **of each** **session**?

|  | Too short  1 | The right length  2 | Too long  3 |
| --- | --- | --- | --- |
| Please select one option: |  |  |  |

What did you think about the **frequency** **of each** **session (weekly)**?

|  | Not often enough  1 | The right frequency  2 | Too often  3 |
| --- | --- | --- | --- |
| Please select one option: |  |  |  |

How many of the **7 sessions** were you able to attend?

|  | 1 | 2 | 3 | 4 | 5 | 6 | 7 |
| --- | --- | --- | --- | --- | --- | --- | --- |
| Please select one option: |  |  |  |  |  |  |  |

How did you feel about the timing of the sessions (i.e., taking place on a weekday and between 9 and 5)?

How did you find the **amount** **of** **content** in each session?

|  | Too little content  1 | The right amount of content  2 | Too much content  3 |
| --- | --- | --- | --- |
| Please select one option: |  |  |  |

How easy did you find the **content to understand?**

|  | Not easy at all  1 | Sometimes easy  2 | Very easy  3 |
| --- | --- | --- | --- |
| Please select one option: |  |  |  |

How did you find the **number** **of** **between-session activities** you were given?

|  | Too few activities  1 | The right number of activities  2 | Too many activities  3 |
| --- | --- | --- | --- |
| Please select one option: |  |  |  |

Did you find the **between-session activities helpful**?

|  | Not helpful at all  1 | Sometimes helpful  2 | Very helpful  3 |
| --- | --- | --- | --- |
| Please select one option: |  |  |  |

How many women were in your group overall? (not including the two facilitators)?

What did you think about this **group size (i.e., the number of women in the group)?**

|  | Too small  1 | The right size  2 | Too big  3 |
| --- | --- | --- | --- |
| Please select one option: |  |  |  |

How helpful was it attending the sessions with **others who have had breast cancer**?

|  | Not helpful at all  1 | Sometimes helpful  2 | Very helpful  3 |
| --- | --- | --- | --- |
| Please select one option: |  |  |  |

How helpful were the **group facilitators (i.e., the duo who ran the sessions?)**

|  | Not helpful at all  1 | Sometimes helpful  2 | Very helpful  3 |
| --- | --- | --- | --- |
| Please select one option: |  |  |  |

Did you find the programme being **run online an issue?** (e.g., technical issues, challenges communication with others?)

|  | Wasn’t an issue at all  1 | Was sometimes an issue  2 | Was a large issue throughout  3 |
| --- | --- | --- | --- |
| Please select one option: |  |  |  |

If one of the people **delivering the programme was a man**, how comfortable did you feel throughout the sessions?

|  | Not at all comfortable  1 | 2 | 3 | 4 | Very comfortable  5 |
| --- | --- | --- | --- | --- | --- |
| Please select one option: |  |  |  |  |  |

If two women delivered the programme, would having had a **man (as a psychologist or cancer support specialist) stopped you** from attending the programme?

|  | Would have stopped me  1 | 2 | 3 | 4 | Would not have stopped me  5 |
| --- | --- | --- | --- | --- | --- |
| Please select one option: |  |  |  |  |  |

Would you like to expand on or explain any of the above answers?

Is there any other feedback you have on the programme, or anything we could do better?

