We will collect a variety of different type of data exploring acceptability and feasibility. This will inform the design of a future definitive RCT and help refine intervention, recruitment, and retention procedures. Figure 1 provides an outline of participant flow in the study and Table 1 provides an outline of the different assessments and their associated timepoints.

- - 1. **Quantitative measures of feasibility and acceptability**

We will collect the following quantitative data to assess feasibility and acceptability of the research design and ABC:

- - - 1. **Monitoring data**
- Rates of recruitment (and associated response rates), with attention to the method by which women were recruited and their demographic diversity.
- Rates of retention following randomisation:
  - Proportion completing ABC (number of sessions attended and between-session activities completed)
  - Proportion of control arm reading the Macmillan body image booklet (plus percentage of booklet read)
  - Proportion completing outcome measures at each assessment (plus data completeness rates; outcome measures described in 5.6.3).
    - 1. **Self-report rating scales included in outcome assessments (see 5.6.3)**
- Rating scales to explore acceptability of ABC (e.g., the group format, online nature, between-session activities; Appendix 9) - to be completed by ABC participants in the immediate post-intervention assessment, i.e., Week 9.
- A single rating scale examining how helpful participants found the ABC programme will also be included in the three- and six-month follow up assessments (see Appendix 31). This will allow monitoring of how participants’ perceptions of the programme and its impacts may develop over time.
- Rating scales to explore acceptability of the research process generally (e.g., information provided about the study, randomisation process, questionnaires; Appendix 10) – to be completed by all participants in the six-month post-intervention assessment i.e., Week 32.
  - 1. **Qualitative measures of feasibility and acceptability**

In addition to the above, we will collect the following qualitative data to assess feasibility and acceptability of the research design and ABC:

- - - 1. **Open-ended questions included in outcome assessments (see 5.6.3)**

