Descriptive analyses (i.e., percentages and confidence intervals) will be conducted on numbers relating to recruitment (including numbers of eligible women who decide not to proceed after reading the PIS) and retention following randomisation, including numbers who complete ABC (i.e., number of sessions attended and between-session activities completed), who read the Macmillan body image booklet (in the control arm; including percentage of booklet read), and who complete self-report outcome measures at each assessment timepoint (including data completeness rates). We will assess the extent of missing data, withdrawals and loss-to-follow-up.

We will report data in line with the Consolidated Standards of Reporting Trials (CONSORT) 2010 Statement showing attrition rates and loss to follow-up.

- - - 1. **Self-report rating scales**

Descriptive analyses (i.e., means, standard deviations, percentages) will be conducted on the ratings scales related to acceptability of ABC (e.g., the group format, online nature, between-session activities; Appendix 9), as well as those related to acceptability of the research process generally (e.g., information provided about the study, randomisation process, questionnaires; Appendix 10).

- - 1. **Analysis of qualitative data**
       1. **Open-ended questions**

The responses to the open-ended questions asking for feedback on ABC (e.g., the group format, online nature, between-session activities; Appendix 9) and the research process generally (e.g., information provided about the study, randomisation process, questionnaires’ Appendix 10) will be analysed in NVivo using thematic analysis (Braun & Clarke 2006). The analytic process of ‘codebook’ thematic analysis will be used (Braun & Clarke 2006, 2022), whereby text will be coded using a priori codes and themes relating to feasibility and acceptability (informed by O’Cathain et al 2015).

- - - 1. **Interviews**

Interviews will be digitally recorded, transcribed verbatim, and analysed in NVivo using thematic analysis (Braun & Clarke 2006). The analytic process of ‘codebook’ thematic analysis will be used (Braun & Clarke 2006, 2022), whereby transcripts will be coded using a priori codes and themes relating to feasibility and acceptability (informed by O’Cathain et al 2015).

- 1. **Analysis of self-report outcome measures**

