**12.31: Appendix 31: Follow-up ABC Acceptability Questions**

Your thoughts about the ABC programme and its impacts may have changed over the last few months. Therefore, reflecting on how you feel now, how **helpful** did you find the programme overall?

|  | Not at all helpful  1 | 2 | 3 | 4 | Very helpful  5 |
| --- | --- | --- | --- | --- | --- |
| Please select one option: |  |  |  |  |  |

Would you like to tell us more about this?

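### The Appendix 9 attendance item has no zero, and women who attended no ABC session are asked to rate the programme at T2, T3 and T4 without a not-applicable option

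*Protocol*

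**What the plan says.** The Appendix 9 feedback form is, under Section 5.6.1.2, "to be completed by ABC participants in the immediate post-intervention assessment, i.e., Week 9". It opens with "Now that you have finished attending" and goes straight to ratings of overall helpfulness, the CBT approach, and the length and frequency of sessions. Only then does it ask how many of the 7 sessions women "were you able to attend". The answer row runs from 1 to 7. Ratings of content, between-session activities, group and facilitators follow. The printed form has no skip instruction and no not-applicable option for a woman who attended nothing.

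Appendix 31, scheduled in Table 1 for T3 and T4, begins "Your thoughts about the ABC programme and its impacts may have changed over the last few months". It repeats the overall helpfulness rating on a scale of 1 to 5, followed by an optional comment.

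Attendance has a second source. Section 8.1 states: "Anonymised data related to ABC attendance and engagement, as well as recordings of the sessions, will be collected by programme facilitators". Section 5.6.1.1 lists sessions attended as monitoring data, separately from the self-report scales in 5.6.1.2. Section 7 analyses it descriptively, with retention after randomisation.

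**The concern.** The attendance item cannot take a value that the protocol itself foresees. Section 5.6.2.2 plans interviews with women who drop out immediately after randomisation, and the Appendix 12 schedule probes the wait to attend ABC as a reason. Appendix 9 also indicates that sessions are held on weekdays between 9 and 5. A woman could therefore miss every session and still return her T2 questionnaire.

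The stake is interpretability. Adherence and the acceptability of online delivery are a stated objective (Section 2), and the ratings are to be summarised by means, standard deviations and percentages. If non-attenders cannot be recognised on the form, a blank has two possible meanings, and a rating may come from someone with no experience of what she is rating.

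**Working it through.** The protocol gives no figure on this point, so there is nothing to reproduce. The check sets the relevant places side by side and then works out what a blank can and cannot tell the analyst.

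1. **Range of the item against range of the quantity.** Sessions attended can be 0 to 7, which is eight values. The Appendix 9 item allows 1 to 7, which is seven. The missing value is non-attendance.

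2. **Comparison with the booklet item.** Appendix 10 asks how much of the Macmillan booklet was read and includes an option for none. It limits the helpfulness rating to those who read some of it and asks non-readers why. Zero exposure can thus be recorded, routed and explained for the booklet but not for ABC. This looks like an oversight and not a choice.

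3. **What a blank means.** Among women in the ABC arm who return T2, let b be the number leaving the item blank, z the non-attenders and n the attenders who simply did not answer. If nobody answers wrongly, b = z + n, so z can lie anywhere from 0 to b. As a share of the 60 women planned for the arm, the range is 0 to b/60. With assumed values of b:
   - b = 3: 0 to 3/60 = 0% to 5%
   - b = 6: 0 to 6/60 = 0% to 10%
   - b = 9: 0 to 9/60 = 0% to 15%

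   If some non-attenders tick 1 instead, even the upper limit b no longer holds. With a '0' option, z is observed directly among those who answer.

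4. **The ratings.** A non-attender who skips the ratings looks like any other missing response. One who answers is pooled with attenders. The direction of any effect on the mean is not determined: she might give a low score, a neutral score or none.

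5. **The facilitators' record.** Suppose, for illustration only, that 6 of 60 women attend nothing and the other 54 average 6 sessions. Total attendances are 54 × 6 = 324, and the mean over all allocated is 324/60 = 5.4. That figure is correct whether or not the record carries IDs. Without IDs, the record would not show how many women, or which, had zero sessions.

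**The case against.** The strongest reply is that Appendix 9 is not the stated source of adherence. Sessions attended is monitoring data, facilitators collect attendance, and nothing says adherence will be computed from the feedback form. This stands. It is not conclusive about the source, because the same monitoring list includes the share of the booklet read, for which the only quantitative instrument shown is the self-report item in Appendix 10. But it does prevent any claim that the Appendix 9 item drives the adherence result.

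A reader might infer more: that non-attenders cannot be recorded at all because the facilitators' data are called anonymised, and so adherence must be overstated. The documents do not support this. The data management plan (Appendix 29, Q6) uses 'anonymised' to mean free of personal identifiers, and questionnaire data described in the same way are matched over time by a participant code. A record keyed to participant ID is compatible with that usage. The Study Manager and CI know each woman's allocation (Section 5.4), so with such a record an allocated woman with no entry is a zero. Overstatement would arise only if completion were computed among those answering Appendix 9, or if non-attenders were left out of the denominator. The protocol states neither.

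It is also fair to say that participants may skip any question (Section 9, care during and following the study), so no false answer is forced. Reasons for non-attendance can surface in the interviews or the free-text boxes, and the printed appendix does not show whether the online version has routing. These points reduce the harm. They do not remove the ambiguity of a blank: interviews cover only 16 to 20 participants, and paper completion is offered, where any routing has to be printed.

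**Conclusion.** The point holds as a defect of the forms, small and cheap to repair. The Appendix 9 item omits a foreseeable value, and the ratings at T2, T3 and T4 have no path for a woman who did not receive the programme. Self-reported attendance and acceptability therefore cannot distinguish non-attenders from item non-response. This matters because the item is the only attendance measure that the protocol shows attached to a participant's own coded questionnaire.

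The size is unknown. It depends on how many women attend nothing yet return questionnaires, for which the protocol gives no figure; the ranges above rest on assumed counts. No bias in overall adherence, and no direction of bias in the ratings, is shown. The identifier on the facilitators' record and the denominator for adherence are matters for clarification, and a statistical analysis plan that is not at hand may settle them.

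**What to change.** In Appendix 9, add '0' to the attendance item, move it ahead of the programme ratings, and route women answering 0 past those ratings to a free-text question on why they did not attend. Print the skip instruction on the paper version as well as programming it online. In Appendix 31, add a 'did not attend' option to the helpfulness rating.

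Two clarifications would help but are not part of the defect: say in Section 8.1 whether the facilitators' record carries the participant ID, and state that sessions attended (0 to 7) will be reported over all women allocated to ABC.

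The cost is one response option and one skip rule in Appendix 9, one option in Appendix 31, and the amendment needed to change the forms. If either form is already in use, record which version each woman completed so that blanks on the old form are not read as answers on the new one.
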